# Comparing the feasibility, acceptability, clinical-, and cost-effectiveness of mental health e-screening to paper-based screening on the detection of depression, anxiety, and psychosocial risk in pregnant women: a study protocol of a randomized, parallel-group, superiority trial

**DOI:** 10.1186/1745-6215-15-3

**Published:** 2014-01-02

**Keywords:** Psychosocial assessment, Online, Screening, Pregnancy, Depression, Anxiety, Stress, Randomized controlled trial

## Abstract

**Background:**

Stress, depression, and anxiety affect 15% to 25% of pregnant women. However, substantial barriers to psychosocial assessment exist, resulting in less than 20% of prenatal care providers assessing and treating mental health problems. Moreover, pregnant women are often reluctant to disclose their mental health concerns to a healthcare provider. Identifying screening and assessment tools and procedures that are acceptable to both women and service providers, cost-effective, and clinically useful is needed.

**Methods/Design:**

The primary objective of this randomized, parallel-group, superiority trial is to evaluate the feasibility and acceptability of a computer tablet-based prenatal psychosocial assessment (e-screening) compared to paper-based screening. Secondary objectives are to compare the two modes of screening on: (1) the level of detection of prenatal depression and anxiety symptoms and psychosocial risk; (2) the level of disclosure of symptoms; (3) the factors associated with feasibility, acceptability, and disclosure; (4) the psychometric properties of the e-version of the assessment tools; and (5) cost-effectiveness. A sample of 542 women will be recruited from large, primary care maternity clinics and a high-risk antenatal unit in an urban Canadian city. Pregnant women are eligible to participate if they: (1) receive care at one of the recruitment sites; (2) are able to speak/read English; (3) are willing to be randomized to e-screening; and (4) are willing to participate in a follow-up diagnostic interview within 1 week of recruitment. Allocation is by computer-generated randomization. Women in the intervention group will complete an online psychosocial assessment on a computer tablet, while those in the control group will complete the same assessment in paper-based form. All women will complete baseline questionnaires at the time of recruitment and will participate in a diagnostic interview within 1 week of recruitment. Research assistants conducting diagnostic interviews and physicians will be blinded. A qualitative descriptive study involving healthcare providers from the recruitment sites and women will provide data on feasibility and acceptability of the intervention. We hypothesize that mental health e-screening in primary care maternity settings and high-risk antenatal units will be as or more feasible, acceptable, and capable of detecting depression, anxiety, and psychosocial risk compared to paper-based screening.

**Trial registration:**

ClinicalTrials.gov Identifier: NCT01899534.

## Background

### Introduction

Depression and anxiety are among the most common morbidities in pregnancy and postpartum (up to 1 year post-delivery), with prevalence rates of 13% to 29% [1-3]. Without early screening and treatment, 50% to 70% of women with prenatal anxiety or depression symptoms [4] will experience persistent symptoms through their child’s early years [5,6] with enduring effects on their children’s development and mental health [7-9]. Psychiatric illness is also the leading cause of maternal mortality in Western countries [10]. However, perinatal mental health problems are severely underdetected and undertreated [11,12]. Without standardized screening, 80% of cases remain undetected [13,14].

While screening is important, there are significant barriers that prevent the majority of pregnant and postpartum women from seeking mental healthcare and disclosing concerns. These include the stigma of mental health, lack of understanding of whether symptoms are abnormal or a typical pregnancy experience, having providers or support persons underestimate their symptoms and concerns, and fear that reporting symptoms will lead others to think that they will be an incompetent mother, prevent the majority of pregnant and postpartum women from seeking mental healthcare and disclosing concerns [15-19]. Although such barriers may prevent women from accessing support on their own, only 4% of women refuse mental health screening when offered by healthcare providers [20,21].

Despite recommendations [22,23] and high acceptance by women [24-26] and providers [27-30], only 20% of perinatal providers conduct proactive screening as part of prenatal care [31] and less than 15% of pregnant/postpartum women receive the help they need [32]. A systematic review conducted by our team (manuscript in preparation) found that substantial personal and system barriers to routine screening exist for healthcare providers, including fear of women’s responses to screening, lack of time, lack of accurate assessment tools and knowledge of their interpretation, and lack of referral processes and options [20,33,34].

Taken together, this body of research underscores the need to identify screening and assessment tools and procedures that are acceptable to both women and service providers, overcome barriers to implementation, and are cost-effective and clinically useful. The most effective perinatal mental health screening and management programs are those characterized by screening incorporated into routine care with designated systems of referral and treatment that are initiated immediately after screening [35].

#### *The potential impact of e-screening*

Routine, standardized screening significantly improves detection of mental health problems [13,14]. However, the scarcity of human health resources poses a major deterrent to routine screening. E-screening has the potential to increase efficiency of mental healthcare by reallocating limited human resources where they are most needed - in-depth follow-up assessment, referral, and treatment. It is a low-resource option [36,37] that can be embedded in current prenatal and postpartum care across various settings and providers (for example, midwives, nurses, obstetricians, family physicians) and thus will increase access to routine screening.

Importantly, e-screening can address the most prominent barriers to screening identified by pregnant women and healthcare providers. Several studies report that e-screening for sensitive issues such as prenatal/postnatal intimate partner violence [38-40] and postpartum depression [41] is acceptable and feasible. It is well-suited for busy clinical settings in that it offers consistency, can be tailored to patient needs, can be used with audio/video for low literacy, provides real-time data [36,37], achieves similar or greater rates of disclosure compared to interviews, and is preferred by patients due to its anonymity [37,38,42,43]. To date, no studies have evaluated e-screening in pregnant women, yet screening that increases access to early prenatal intervention may reduce the risk of prenatal and postpartum depression/anxiety, as well as adverse child outcomes. One small study that examined the psychometric properties and rates of detection of postpartum depression of two Internet-based screening tools found that both tools (Edinburgh Postnatal Depression Scale; The Postpartum Depression Screening Scale) had excellent validity and reliability with prevalence rates within range of other self-report and interview-based assessment approaches [41].

There is a clear need for a rigorous evaluation of the feasibility, acceptability, and psychometric performance of e-screening for prenatal mental health difficulties. A key consideration for evaluation is to determine whether established assessment tools are valid and reliable for use when delivered online. For example, it has been shown that some tools have different psychometric properties when delivered online, suggesting a need for different cutoff points [44]. Another key issue is the inclusion of women experiencing a broad range of degrees of psychosocial risk. Pregnant women with high-risk pregnancies represent a vulnerable group in that the prevalence of mental health problems in this group is more than three times greater than medically low-risk women [45,46]; however, medically high-risk women are rarely included in intervention studies of perinatal mental health.

#### *Screening versus psychosocial assessment*

Screening is defined as the use of a symptom-based tool, and psychosocial assessment is the combined use of a screening tool plus an assessment of psychosocial risk factors [3]. In this protocol, e-screening refers to use of the Internet to collect and transfer data from a psychosocial assessment.

## Purpose

### Objectives, research questions, and hypotheses

#### *Primary objective*

The primary objective of the study is to determine pregnant women’s and healthcare providers’ views of the feasibility and acceptability of mental health e-screening compared to paper-based screening.

#### *Secondary objectives*

The five secondary objectives are to compare the two modes of screening on: (1) the level of detection of prenatal depression and anxiety symptoms and psychosocial risk; (2) the level of disclosure of symptoms; (3) the factors associated with the acceptability, feasibility, and disclosure; (4) psychometric properties (sensitivity, specificity, positive and negative predictive values) of the e-version of the Antenatal Psychosocial Health Assessment (ALPHA) and Edinburgh Postnatal Depression Scale (EPDS) when administered to medically low- and high-risk pregnant women; and (5) cost-effectiveness of screening.

### Research questions and hypotheses

The specific research questions and hypotheses corresponding to the primary and secondary objectives are described in Table 1. Overall, we hypothesize that mental health e-screening in primary care maternity settings and high-risk antenatal units will be as or more feasible, acceptable, and capable of detecting depression, anxiety, and psychosocial risk compared to paper-based screening.

**Table 1 T1:** Primary and secondary objectives, research questions, and hypotheses

**a**				
**Primary objective**	**Research question**	**Outcome**	**Measures**	**Testable hypothesis**
To compare the feasibility and acceptability of mental health e-screening *versus* paper-based screening.	Is mental health e-screening as or more feasible and acceptable to pregnant women and their healthcare providers than paper-based screening?	Feasibility: % women in intervention and control groups reporting that screening is easily done as a component of routine prenatal care; mean CAE score	Quantitative:	Mean CAE scores and % of women responding affirmatively to questions of feasibility and acceptability will be similar or significantly higher in the intervention group (indicating greater feasibility/acceptability) compared to the control group
			Feasibility	
			Example (CAE): I liked/would like using the tablet to answer these questions	
		Acceptability: % of participants in intervention and control groups reporting that screening is acceptable; % of participants reporting that questions about emotional health were easy to understand and easy to navigate around on the tablet	Acceptability	
			Example: (1) I did not/would not like answering questions on a tablet because it felt/would feel impersonal	
			Qualitative:	
			Semi-structured interviews	
**b**				
**Secondary objective**	**Research question**	**Outcome**	**Measure**	**Testable hypotheses**
1. To compare the level of detection of symptoms of prenatal depression, anxiety, and psychosocial risk in e-screening *versus* paper-based screening	Compared to paper-based screening, what is the effect of mental health e-screening in pregnant women on the detection of prenatal depression, anxiety, and psychosocial risk?	Proportion of women scoring above cutoff point of EPDS for depression and anxiety; proportion of women identified as some or high psychosocial risk on ALPHA	EPDS	Compared to the control group, a higher proportion of women in the intervention group will: (1) score 13 or more on the total EPDS (corresponding to probable prenatal depression); (2) score 4 or more on the anxiety subscale of the EPDS (Q3, 4, 5) (corresponding to probable prenatal anxiety); and (3) be identified as having some/moderate or high psychosocial risk on the ALPHA
			ALPHA	
2. To compare the level of disclosure of symptoms of prenatal depression and anxiety, and psychosocial risk in e-screening *versus* paper-based screening	Compared to paper-based screening, what is the effect of mental health e-screening in pregnant women on the disclosure of prenatal depression, anxiety, and psychosocial risk?	Level of disclosure: Mean subscale scores: (1) risk of disclosure; (2) benefits of disclosure	DES	Compared to paper-based screening, e-screening promotes greater disclosure (for example, the mean score risk of disclosure is significantly lower and benefit of disclosure is significantly higher in the e-screening group)
3. To determine factors associated with the acceptability and feasibility of mental health e-screening as well as disclosure	What factors are associated with acceptability and feasibility of mental health e-screening in pregnant women?	Identification of factors that significantly increase odds of acceptability and feasibility of e-screening	Quantitative: (1) Demographic variables (age, gestation, marital status; ethnicity); (2) mental health history; current mental health status; EPDS scores; ALPHA category; (3) DES scores; (4) medical risk; (5) features of the screening instrument/process	Factors that are significantly associated with acceptability and feasibility: mental health history, current mental health status (EPDS, ALPHA), disclosure (DES), medical risk; features of screening instrument
			Qualitative:	
			Semi-structured interviews	
				Factors not associated: demographics
4. To compare the psychometric properties (sensitivity, specificity, cutoff points) of paper-based ALPHA and EPDS *versus* the e-version administered to medically low- and high-risk pregnant women	Are the psychometric properties (for example, sensitivity, specificity, cutoff points) similar or better in the ALPHA and EPDS e-version compared to the paper-version when administered to pregnant women?	Psychometric properties: sensitivity, specificity of ALPHA and EPDS in paper-based and e-versions	ALPHA, EPDS, MINI	The psychometric properties of e-version of ALPHA and EPDS are similar or better compared to paper-based version
5. To compare the cost-effectiveness e-screening compared to paper-based screening	Is e-screening as a component of routine prenatal care cost effective when compared to paper-based screening?	Cost-effectiveness: actual costs	The expected incremental cost effectiveness of e-screening is cost effective at values of health considered acceptable in the Canadian healthcare system	E-screening will be cost effective

ALPHA: Antenatal Psychosocial Health Assessment; CAE: CASI Assessment Evaluation; DES: Disclosure Expectations Scale; EPDS: Edinburgh Postnatal Depression Scale; MINI: Mini International Neuropsychiatric Interview.

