## Methods/Design

### Study design

The study is a parallel-group, randomized, controlled superiority trial (RCT) with a qualitative descriptive component (Figure 1). This design is well-suited for answering questions of effectiveness, acceptability, and feasibility [47]. In this trial, physicians and all research assistants conducting diagnostic interviews are blinded. We adhered to CONSORT guidelines in the design of the trial [45,46] and the SPIRIT guidelines [48,49] in reporting its details in this protocol. Approval for this study was granted by the Human Research Ethics Board at the University of Alberta.

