#### Sample size

##### 

**Determination of sample size** Because no data are available to guide estimation of a minimal clinically important difference in ‘true’ cases detected through e-screening a ‘confidence interval (CI) approach’ [56] was used. Based on high levels of acceptability and disclosure reported using computer screening [39,40], e-screening would be feasible if, in the intervention group: (1) 85% of women indicated that they were able to tell the truth on all items (Q7 CAE); (2) 85% scored 4 to 8 on the Risk subscale of the DES (no/slight perceived risk to disclosure); and (3) 85% scored 16 to 20 on the DES Utility subscale (for example, disclosure moderately or very beneficial). The sample size calculation (Table 2) indicates that 261 women per group (*n* = 522) is required.

**Table 2 T2:** Sample size determination

**Using the calculation of a confidence interval for a proportion, a 95% CI and a margin of error of 0.05:**	**Accounting for an estimated attrition/loss to follow-up of 25% based on other reported rates in pregnant and postpartum women (55,66):**
p = a priori estimate of % of interest; *n* = sample size	*n* = total sample size; L = attrition rate + loss-to-follow up
*n* = p(1-p) [1.96/.05]^2^	N_new_ = n/(1-L)
*n* = 0.85(1–0.85) [39.2]^2^	N_new_ = 196/(1–0.25)
*n* = 196	N_new_ =261

Therefore a minimum of 261 women per group would be required.

##### 

**Feasibility of achieving sample size** The maternity clinics conduct initial prenatal visits for a total of 50 women per month across all clinics. The number of new patients on the high-risk antenatal unit is similar at 45 women per month. Clinic staff estimates that roughly 4% of women would be ineligible due to language (96% eligible = 91 women per month). A conservative estimation of 50% participation rate [57,58] would yield 46 women per month. Thus, recruitment of women is expected to take 12 months.

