### Analysis

#### *Primary outcome and description of sample*

Intention-to-treat analysis will be conducted for all analyses. We will use descriptive data (frequencies/95% CI; means/standard deviation) to describe the sample. Baseline differences in groups will be compared using independent t-tests (means) and chi-square tests (%) to determine the extent to which randomization was successful. Statistical significance for all analyses is set at *P* <0.05. We will use two-tailed independent t-tests to compare intervention and control group differences in mean scores of the CAE and chi-square tests to compare proportions of women in each group responding affirmatively to questions on feasibility and acceptability.

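### The stated superiority tests cannot establish the primary hypothesis of similar or better feasibility and acceptability, and the one-arm sample size, given as both 522 and 542, does not fill the gap

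*Protocol article*

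**What the plan says.** - **Design label.** Study design: "The study is a parallel-group, randomized, controlled superiority trial (RCT) with a qualitative descriptive component".
- **Primary hypothesis.** Table 1a expects that mean CAE scores and the percentage of women responding affirmatively to "questions of feasibility and acceptability will be similar or significantly higher in the intervention group". The overall hypothesis, in Research questions and hypotheses and again in the Abstract, is that e-screening "will be as or more feasible, acceptable, and capable of detecting depression, anxiety, and psychosocial risk compared to paper-based screening".
- **Primary analysis.** Under Analysis: "We will use two-tailed independent t-tests to compare intervention and control group differences in mean scores of the CAE", with chi-square tests for the proportions. Significance is set at P<0.05 throughout.
- **Sample size.** The article says it uses a confidence-interval approach because no data guide a minimal important difference in true cases detected. It says that "e-screening would be feasible if, in the intervention group" 85% meet each of three criteria: one CAE item on truthfulness and two score bands on the Disclosure Expectations Scale (DES). Table 2 ends: "Therefore a minimum of 261 women per group would be required". The text gives 522 in all.
- **Abstract.** "A sample of 542 women will be recruited from large, primary care maternity clinics" and a high-risk antenatal unit.

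**The concern.** A claim that the tablet is as good as or better than paper is a non-inferiority claim. It needs a stated largest acceptable deficit and a confidence interval that rules that deficit out. A two-tailed difference test can show that the arms differ, but failing to show a difference does not show that they are alike.

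As the article stands, only a significantly lower result in the tablet arm would clearly refute the primary hypothesis. A materially worse tablet could leave it apparently intact. The sample size does not help, because it contains neither a between-arm difference nor a power term. A reader therefore cannot tell what deficit the trial could exclude, or how many women it means to enrol.

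**Working it through.** **1. The plan's own size.** Inputs from Table 2: p = 0.85, margin of error 0.05, attrition 25%.
- n = 0.85 × 0.15 × (1.96/0.05)² = 0.1275 × 39.2² = 195.92, so 196.
- 196/(1 − 0.25) = 261.33, given as 261; 2 × 261 = 522.

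The figures reproduce. They describe one proportion in one arm.

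**2. The total of 542.** It exceeds 522 by 20. With 196 evaluable per arm it would need attrition of 1 − 392/542 = 27.7%, which is not stated. The roughly 20 women interviewed qualitatively are a subset of participants (Outcomes and measurement, Acceptability), so they do not account for the gap.

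**3. Between-arm precision.** Assume 85% in both arms. The 95% half-width for the difference is 1.96 × √(2 × 0.1275/n).
- n = 196: 1.96 × 0.03607 = 7.1 points.
- n = 261: 1.96 × 0.03126 = 6.1 points.

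**4. Chance that a real deficit is non-significant.** Assume 85% on paper and 80% on tablet, so the pooled rate is 0.825. Power ≈ Φ[(0.05 − 1.96 × SE₀)/SE₁], where SE₀ = √(2 × 0.825 × 0.175/n) and SE₁ = √((0.1275 + 0.16)/n).
- n = 196: SE₀ = 0.03838, SE₁ = 0.03830; Φ(−0.659) = 0.255. Non-significant in about 74% of trials (0.74496 unrounded).
- n = 261: SE₀ = 0.03326, SE₁ = 0.03319; Φ(−0.458) = 0.324. Non-significant in about 68%.

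**5. Margin the existing size could support.** Assume 85% in both arms and one-sided 0.025. Power = Φ(margin/SE − 1.96), with SE from step 3.

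| Margin | 196 per arm | 261 per arm |
|---|---|---|
| 5 points | 28% | 36% |
| 7.5 points | 55% | 67% |
| 10 points | 79% | 89% |

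Allowing for 25% attrition, 80% power needs 2,136 recruited for 5 points, 950 for 7.5 points and 536 for 10 points.

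**6. The 85% criteria.** The truthfulness item could fall under the chi-square comparison of affirmative answers. The two DES bands have no stated analysis: the Disclosure paragraph compares subscale means, and the factors analysis splits at the 75th percentile.

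**The case against.** - **The article never says that P>0.05 will be read as equivalence.** A reader might infer that it will, but that is a prediction about reporting. A rule could also sit in an analysis plan not shown here. This stands, and a missing margin alone would not be a finding. What remains is that the hypothesis, the label and the tests are all stated in the article and do not fit together.
- **A precision-based size is legitimate for a feasibility question, and the article declares it openly.** This also stands. The arithmetic is right for what it computes, and the size does imply a between-arm precision; the article just does not report it.
- **261 per group is called a minimum.** So 542 could be a deliberate higher target, and expected recruitment (46 × 12 = 552) covers either figure. It is therefore an unexplained discrepancy and not a proven contradiction, but no passage says which total governs.
- **A margin on the CAE would not help.** Control women answer adapted CAE items about using a tablet, so both arms rate the tablet. A small difference there cannot show parity with paper. This stands and limits the remedy.
- **Smaller points a reader might add do not matter.** Rounding 261.33 down leaves 195.75 evaluable. Applying 25% attrition to items answered in the randomization session only enlarges the sample.

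**Conclusion.** The concern holds in this form: the primary hypothesis includes a parity claim that the stated tests cannot establish, and the sample size was not built for the between-arm comparison. A 5-point deficit would go undetected in about 74% of trials (196 per arm) or 68% (261). Between-arm precision is ±7.1 to ±6.1 points, against the ±5 points stated for one arm.

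These figures assume 85% acceptability on paper. That rate is borrowed from the sample-size section, where it refers to truthfulness and DES scores in the intervention arm; the article gives no acceptability rate for paper. The margins are illustrative, since the documents state none. The documents do not support saying that the investigators intend to treat non-significance as equivalence, or that the calculation behind 522 is wrong.

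**What to change.** 1. **Choose one framework before data are seen.**
   - *Superiority only:* delete the parity wording from the Abstract, the overall hypothesis and Table 1a. This costs text alone. Say plainly that, from 85% on paper, 80% power requires about 93.7% on tablet (196 per arm) or 92.7% (261).
   - *Non-inferiority, then superiority:* state and justify a margin, and conclude that the tablet is as acceptable only if the 95% confidence interval for the difference in acceptability proportions excludes it. Use items on which each woman rates the form she completed, and do not use the CAE as evidence of parity with paper. The cost depends on the margin: near 10 points the existing size gives 79–89% power; at 5 points it gives 28–36%, and the trial would have to be far larger or the claim dropped.
2. **Restate the Sample size section:** ±5 points within the intervention arm, about ±6 to ±7 points between arms.
3. **Give one total throughout,** with the reason if it is 542.
4. **Report the intervention-arm proportions for the 85% criteria with 95% confidence intervals,** at least for the two DES bands. Do not attach a pass rule such as a lower limit above 80%: with 196 women and the normal interval it needs 167 successes, which happens only 52% of the time if the true rate is 85%.

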### Secondary outcomes

The five secondary outcomes are (see measures in Table 1b):

(1) the proportion of pregnant women scoring 13 or more on the total EPDS, 4 or more on the anxiety subscale, and identified as some or high psychosocial risk on the ALPHA;

(2) the level of disclosure as assessed by mean scores on the Perceived Risk and Perceived Utility subscales of the Disclosure Expectations Scale (DES) [55]. The DES is an 8-item scale designed for evaluation of the perceived risk (items 1, 2, 4, and 5) and benefit (items 3, 6, 7, and 8) of disclosure. Convergent validity of the subscales has been demonstrated with other measures of self-disclosure, as well as psychological distress, and intention to seek mental healthcare [55];

(3) description of factors that significantly increase the odds of acceptability, feasibility, and disclosure related to each form of screening;

(4) psychometric properties (for example, Cronbach’s alpha, sensitivity, specificity, positive and negative predictive values) of the e-version of the EPDS and ALPHA. A scoring algorithm does not currently exist for the ALPHA (for example, the trained provider subjectively judges risk based on responses); however, an algorithm would promote standardization in clinical decision-making and efficiency since a score could be calculated as part of e-screening. We plan further tool development comprising derivation of a quantitative scoring method for classifying women into psychosocial risk categories; and

(5) cost-effectiveness of detecting clinical depression and anxiety in e-screening *versus* usual screening (that is, equipment and human resource costs of e-screening *versus* paper-based - see Secondary outcomes).

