#### *Secondary outcomes*

##### 

**Detection** Differences in proportions of women in the control and intervention group scoring 13 or more on the EPDS, and categorized as some or high-risk on the ALPHA will be estimated using chi-square tests.

##### 

**Disclosure** Comparison of mean scores of the subscales of the DES (risk, benefit of disclosure) will be done using two-tailed independent sample t-tests.

##### 

**Factors associated with acceptability, feasibility, and disclosure** We will use multivariable logistic regression to determine predictors of acceptability, feasibility, and disclosure and report relative risks and 95% CIs. Outcomes will be dichomotized measures of acceptability, feasibility (based on CAE), and disclosure (based on DES) where ‘high’ acceptability, feasibility, and disclosure will include participants whose responses place them above the 75th percentile for the measure. Models will be built using variables that are associated with outcomes at *P* <0.10 on crude analyses, entering demographic variables in a first block, followed by obstetrical factors, mental health history, and the ACES score. Results will be reported as odds ratios and 95% CIs.

##### 

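### Table 1b hypothesises that demographics are not associated with acceptability or feasibility, but the planned analysis can support this only by non-significance and drops the very variables concerned from the model

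*Protocol article*

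**What the plan says.** All references are to the protocol article.

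- **Table 1b, secondary objective 3.** The outcome is "Identification of factors that significantly increase odds of acceptability and feasibility of e-screening". The measures include "Demographic variables (age, gestation, marital status; ethnicity". The testable hypotheses name factors expected to be associated, then add "Factors not associated: demographics".
- **Secondary outcomes, item 3.** The aim is a "description of factors that significantly increase the odds of acceptability, feasibility, and disclosure related to each form of screening".
- **Analysis, Factors associated with acceptability, feasibility, and disclosure.** The 'high' group consists of "participants whose responses place them above the 75th percentile for the measure". On model building: "Models will be built using variables that are associated with outcomes at" a crude P below 0.10, with demographics entered as the first block. Odds ratios with 95% CIs will be reported.
- **Analysis, Primary outcome and description of sample.** "Statistical significance for all analyses is set at *P* <0.05".
- **Sample size.** The only calculation is for the precision of a single proportion. It gives 196 per group, inflated to 261 (522 in total). No association is powered and no margin is stated.

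**The concern.** A statement that a factor is not associated with an outcome is an affirmative claim about the size of an effect. The only stated route to it here is a P-value that misses a threshold, and that is easier to obtain when data are few or a category is rare. Cutting the outcome at the 75th percentile adds to this, because at most about a quarter of women (fewer with ties) are events.

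The entry screen makes it worse. A demographic with crude P of 0.10 or more never enters the model, so no adjusted odds ratio or interval is promised for exactly the variables that would be called not associated.

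At stake is a secondary conclusion: that acceptability and feasibility do not depend on age, gestation, marital status or ethnicity. The Setting section describes the population as sociodemographically diverse, so readers may give weight to such a statement when the data could not exclude a sizeable difference.

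**Working it through.** **The plan's own figure.** n = p(1−p)(1.96/0.05)² = 0.85 × 0.15 × 39.2² = 195.9, rounded to 196. Then 196/(1−0.25) = 261.3, given as 261, and 2 × 261 = 522. This reproduces, but it concerns one proportion only.

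**Inputs from the article.** Alpha 0.05 (two-sided assumed for the regression); entry screen P<0.10; outcome rate about 25% from the 75th-percentile cut; 261 per arm or 522 pooled.

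**Assumptions.** A binary factor with prevalence f of 10% to 50%, a true odds ratio (OR) of 2, and no covariate adjustment.

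**Chance of missing OR = 2.** Solve (1−f)p0 + f·p1 = 0.25 with odds(p1) = 2·odds(p0). Then power = Φ[(p1 − p0 − z·SE0)/SE1], where

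- SE0 = √[0.25 × 0.75 × (1/n1 + 1/n0)]
- SE1 = √[p1(1−p1)/n1 + p0(1−p0)/n0]

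Example, one arm of 261 with f = 10%: n1 = 26.1, n0 = 234.9, p0 = 0.2354, p1 = 0.3811, SE0 = 0.0893, SE1 = 0.0990.

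- At P<0.05: (0.1457 − 1.96 × 0.0893)/0.0990 = −0.30. Power is 38%, so 62% are missed.
- At the P<0.10 screen: (0.1457 − 1.645 × 0.0893)/0.0990 = −0.01. About 50% fail to enter.

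| Factor prevalence | One arm, 261: P≥0.05 | One arm, 261: fails screen | Pooled, 522: P≥0.05 | Pooled, 522: fails screen |
|---|---|---|---|---|
| 10% | 62% | 50% | 38% | 28% |
| 20% | 45% | 33% | 17% | 11% |
| 30% | 36% | 26% | 10% | 6% |
| 50% | 34% | 23% | 8% | 4% |

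A simulation of the Wald and chi-square tests agrees within about two percentage points.

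**Expected 95% CI if the true OR is 1.** The limits are 1/k and k, with k = exp{1.96·√[1/(N·f·0.1875) + 1/(N(1−f)·0.1875)]}.

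- N = 261: 0.39 to 2.54 at f = 10%; 0.57 to 1.75 at f = 50%.
- N = 522: 0.52 to 1.94 at f = 10%; 0.67 to 1.49 at f = 50%.

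In one arm, a typical null result for an uncommon category excludes neither doubled nor halved odds.

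**The error in the other direction.** The hypothesis as written covers four demographics and two outcomes. If all are truly null, the chance of at least one P<0.05 is 1 − 0.95⁸ = 34%, assuming independent tests.

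**What a bound would require (illustration only).** Take an assumed range of 0.5 to 2.0, a true OR of 1, a 95% CI inside the range and 80% power. Then N = [1/(f·0.1875) + 1/((1−f)·0.1875)] × (1.96 + 1.2816)²/(ln 2)². This gives 467 at f = 50%, 556 at 30%, 729 at 20% and 1,296 at 10%. One arm is too small in every case.

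**The case against.** **The relevant sample is not the one left after attrition.** The feasibility, acceptability and disclosure items are answered in the same sitting as the screen, and all fields except income are mandatory (Data collection procedures). The 25% loss therefore has little bearing here. A reader might apply it and conclude, from 196 women per arm, that doubled odds are missed up to 69% of the time. The document does not support that as the working case. This objection stands, and 261 and 522 are used above.

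**Pooling is plausible.** Control women answer adapted items about their views of e-screening, so feasibility could be analysed in both arms together. Power for a common factor is then good. This also stands. However, the wording of secondary outcome 3 points to analysis by form of screening, and the article does not settle which is meant.

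**Odds ratios and 95% CIs are promised.** It would be too strong to say that P-values are all that will be reported. But the promise follows the screened model: entering demographics as the first block does not exempt them from the screen, and no bound is given for reading an interval.

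**Multiplicity can be overstated.** A reader might count eight baseline demographics and three outcomes and reach 1 − 0.95²⁴ = 71%. The hypothesis names four demographics and two outcomes; disclosure appears there as a predictor. The supported figure is 34%.

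**It is secondary, and the SAP may add detail.** This is true and limits the consequence. But the article itself fixes the hypothesis, the screen, the cut and the alpha, so the point is about what is stated rather than what is absent. A reader might also infer that a null result would decide roll-out to particular demographic groups. No passage says so: the Conclusion refers to risk subgroups, and the qualitative component deliberately samples a range of demographic views.

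**Conclusion.** The point holds in a limited form. As written, the hypothesis of no demographic association can be supported only by non-significance, and the entry screen removes from the model the variables it concerns.

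The weakness is material for one-arm analyses, where a doubling of the odds would be non-significant about 34% to 62% of the time and would fail the screen about 23% to 50% of the time. It is also material for uncommon categories in the pooled sample, where about 38% would be missed at 10% prevalence. For factors at 20% to 50% prevalence in the pooled 522, the miss rate is about 8% to 17%, so it would be wrong to say that the trial as a whole cannot see doubled odds.

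These figures rest on assumed factor prevalences, an assumed OR of 2, a 25% outcome rate and unadjusted binary predictors. Continuous age and gestation were not modelled. The matter is worth correcting because the change is cheap, but it touches a secondary hypothesis and not the primary comparison.

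**What to change.** 1. Exempt the Table 1b demographics from the P<0.10 screen and keep all of them in each model.
2. Report every adjusted OR with its 95% CI, whatever its P-value.
3. Give one joint likelihood-ratio test of the demographic block per outcome, in place of a verdict from separate tests.
4. Reword Table 1b so that a non-significant result is reported as *no evidence of association*, together with the range of odds ratios not excluded.
5. Claim *not associated* only if the sponsor states a bound in advance and the 95% CI lies inside it. The choice of bound is the sponsor's; 0.5 to 2.0 above is only an illustration.

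The cost is a change to the analysis text and Table 1b, plus a few more model terms; no extra data are needed. The drawback is that many demographic results will read as inconclusive, particularly in one-arm analyses.
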